**Figure 5. F5:**
[figure not shown]
Gait analysis using a joint motion function testing system. Reflective markers were attached to the participants’ waist, femur, tibia, and foot. Participants walked forward and backward on a treadmill at a speed of 3 km/h for 15 seconds in each direction. Hip, knee, and ankle kinematics, as well as overall gait stability, were evaluated.

**Figure 6. F6:**
[figure not shown]
Plantar pressure assessment using a pressure testing platform. Participants stood and walked on the pressure testing platform to assess foot arch characteristics, inversion/eversion patterns, and plantar force distribution using the gait training and testing software.

### Safety Assessment

A rigorous adverse event monitoring system will be implemented throughout this trial. All adverse events occurring during this study will be recorded in detail, including the time of onset, clinical manifestations, severity, potential causes, and management measures. In the event of an adverse reaction, the clinical investigators will assess the participant’s condition and determine whether continuation in this trial is appropriate. Necessary medical care will be provided, and all serious adverse events will be reported promptly to the Medical Research Ethics Committee of Shanghai Changhai Hospital.

### Statistical Analysis

Statistical analyses will be executed using SPSS (version 27.0), adhering to a two-sided significance threshold of *P*<.05 while reporting effect sizes and 95% CIs where appropriate. Baseline characteristics will be summarized solely through descriptive statistics without formal hypothesis testing, with continuous variables first evaluated for normality and homogeneity of variance to determine their presentation as either mean with SD or median with IQR.

Under an intention-to-treat framework encompassing all randomized participants, missing data patterns will be evaluated and addressed via multiple imputations, the robustness of which will be subsequently verified through sensitivity analyses including per-protocol and complete-case approaches. Primary outcomes will be modeled using linear mixed-effects specifications that will incorporate group, time, and their interaction as fixed effects alongside participant-level random intercepts to account for the repeated-measures design.

For continuous secondary outcomes, analysis of covariance adjusted for baseline values will be used where appropriate, whereas other continuous and categorical variables—the latter summarized as frequencies and percentages—will be scrutinized using parametric, nonparametric, chi-square, or Fisher exact tests depending on data distribution, with false discovery rate adjustments applied throughout to mitigate type I error inflation from multiple comparisons.

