### Sample Size Calculation

The sample size calculation for this study is performed using SPSS (version 27.0) and was based on the primary outcome of the 6-minute walk test (6MWT). According to evidence from previously published randomized controlled trials and systematic reviews in patients with COPD, the minimal clinically important difference (MCID) for 6MWT is approximately 54 m, and the baseline SD is generally reported to range between 70 and 90 m. To ensure a conservative and methodologically robust estimation, an SD of 80 m will be adopted for the present study [37,38].

A two-sided significance level of *α*=.05 and a type II error rate of *β*=.20 (80% power) were specified. Based on an MCID of 54 m, the required sample size is calculated using the following formula: $n=\frac{{\left(Z_{\frac{\alpha }{2}}+Z_{\beta }\right)}^{2}\times 2\times {SD}^{2}}{{MCID}^{2}}$. This yields a minimum sample size of 32 participants per group, for a total of 64 participants across both groups. Accounting for an anticipated dropout rate of 15%, the final required sample size is adjusted to 76 participants, with 38 participants allocated to each group.

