#### 6MWT

6MWT is a widely used method for evaluating exercise capacity in patients with respiratory disorders and for assessing the efficacy of clinical interventions. Previous studies [48,49] have demonstrated that the 6MWT serves as a valid and reliable measure of functional capacity and health-related quality of life in patients with COPD, while also providing an indicator of disease severity. Based on previous findings [37,38], the MCID for 6MWT ranges from 30 to 54 m, and the baseline SD is between 70 and 90 m. This study will use a 6MWT data acquisition system in combination with a dynamic vital signs monitor, CB200 (Contec), for testing. Participants will be instructed to walk back and forth along a 30-meter flat corridor at their maximum tolerable speed for six minutes. Distance markers will be placed every 5 meters to aid measurement. The recording device will capture the total walking distance as well as heart rate and oxygen saturation before and after the test. The 6MWT outcome will serve as a primary indicator of intervention efficacy, assessed in week 0 and week 13.

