### Data Collection and Management

Standardized data collection forms will be developed before this study, incorporating all required variables and outcome measures. Research team members will record and collect data following consistent protocols. All study data will be securely stored in a dedicated database for long-term preservation. Upon study completion, all data and associated documentation will be archived for potential future review.

In the event of missing data, efforts will be made to identify the reasons for data loss and to retrieve missing information whenever possible. The extent and patterns of missing data will be documented and reported. Appropriate statistical methods will be applied to handle missing data during analysis, based on the nature and proportion of missing values, to minimize potential bias and ensure the robustness of this study’s results.

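### Per-protocol and complete-case analyses cannot verify that the imputed 6MWT result is robust to informative dropout

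*Protocol article*

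**What the plan says.** In Statistical Analysis, under an intention-to-treat framework covering everyone randomised, "missing data patterns will be evaluated and addressed via multiple imputations", and the sentence continues: "the robustness of which will be subsequently verified through sensitivity analyses including per-protocol and complete-case approaches". The primary outcomes are analysed with "linear mixed-effects specifications that will incorporate group, time, and their interaction as fixed effects alongside participant-level random intercepts".

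Data Collection and Management adds only a general statement: "Appropriate statistical methods will be applied to handle missing data during analysis, based on the nature and proportion of missing values".

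The 6MWT is "assessed in week 0 and week 13", and Table 1 shows no visit between these two at which it is repeated. On losses, Sample Size Calculation says: "Accounting for an anticipated dropout rate of 15%, the final required sample size is adjusted to 76 participants".

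The article names no missingness assumption, no imputation model and no analysis that departs from missing at random. Compliance Assessment defines good adherence by exercise sessions in the Liuzijue group and by telephone calls in the control group, each with an 85% threshold.

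**The concern.** The article chooses two checks and says what they establish. A sensitivity analysis tests an imputation only if it relaxes the assumption on which the imputation rests. Standard multiple imputation and a likelihood-based mixed model both rest on missing at random. A complete-case analysis rests on that or on something stronger. A per-protocol analysis changes the population and the question.

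The risk is specific to this design. Participants know their allocation, and only one arm is asked to exercise twice daily. Liuzijue participants who leave because of breathlessness, exacerbation or burden could plausibly walk less far at week 13 than their baseline predicts. If so, imputation and complete-case would be biased together, and their agreement could be reported as evidence of robustness.

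**Working it through.** **1. Expected missingness.** The plan's dropout step reproduces: 32/0.85 = 37.6, so 38 per arm. That leaves 38 − 32 = 6 missing per arm, a share of 6/38 = 0.158. (The 32 itself does not follow from the stated formula: 2 × (80 × 2.80/54)² = 34.45, so 35. That is a separate matter, and nothing below rests on it.)

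**2. Why the two analyses agree.** Suppose week-13 distance is imputed from group and baseline. In each arm the imputed values lie, on average, on the completers' regression line with intercept a and slope b. With two visits and completed data, the planned group-by-time interaction is the difference between arms in mean change. The arm mean changes are:

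- imputation: a + (b − 1) × (baseline mean of all randomised)
- complete-case: a + (b − 1) × (baseline mean of completers)

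The difference is (b − 1) × (baseline mean of all − baseline mean of completers), apart from simulation noise. It has no term for the unseen week-13 outcome. The gap can reveal dropout related to baseline. It cannot reveal dropout related to week 13 given baseline.

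**3. Size of an undetected bias.** If Liuzijue dropouts walk D metres less than predicted, the all-randomised effect is overstated by (missing share) × D:

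| D | 6/38 missing | 25% missing (assumed) |
|---|---|---|
| 30 m | 4.7 m | 7.5 m |
| 54 m | 8.5 m | 13.5 m |
| 80 m | 12.6 m | 20.0 m |

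**4. Simulation with the planned contrast.** From the plan: 38 per arm, SD 80 m, effect 54 m before the shift. Assumed: baseline to week-13 correlation 0.7. There were 6 missing per arm and 2,000 trials per row. Mean estimates in metres:

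| Liuzijue dropouts worse by | All-randomised effect | Complete-case | Imputation |
|---|---|---|---|
| 0 | 54.6 | 54.6 | 54.5 |
| 30 | 49.4 | 54.2 | 54.1 |
| 54 | 45.9 | 54.7 | 54.6 |
| 80 | 40.8 | 53.4 | 53.5 |

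The two methods agree on average to 0.1 m in every row, and within a trial they differ by about 2 m. Agreement is the same with no bias as with about 13 m of bias. A heavier assumed mechanism (outcome-dependent dropout, about 27% in Liuzijue and 10% in control, baseline-adjusted analysis) gave imputation 72.7 and complete-case 72.6 against 54.2 with full data. I use that run for the agreement, not for the size.

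**5. Where complete-case does inform.** With baseline-dependent dropout in the Liuzijue arm and the same contrast, imputation gave 53.5 m and complete-case 47.5 m. At slope 0.7, step 2 makes a 6 m gap equivalent to completers' mean baseline lying 6/0.3 = 20 m from that of all randomised.

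**6. Per-protocol.** With completely random dropout, where imputation is unbiased (53.9 m), a per-protocol set gave 65.9 m, because adherence was assumed to select better responders. Its movement away from the imputed result does not diagnose the imputation.

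**7. Scale.** With 32 per arm, 80 × √(2/32) = 20 m. At correlation 0.7 the standard error of the change contrast is 20 × √(2 × 0.3) = 15.5 m, and with baseline adjustment it is 20 × √(1 − 0.49) = 14.3 m. A bias of 5 to 13 m is below either.

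**The case against.** The strongest reply is that this is a condensed article, that the word introducing the two checks leaves the list open, and that shift sizes and tipping points belong in an analysis plan that is not shown. That stands as far as it goes: the absence of delta values is not the fault. What remains is that the article states a role for two named analyses which they cannot fill.

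The second reply is that the imputation model is unspecified. Exercise logs with exertion scores, attendance, telephone contacts and adverse-event records could enter it. This also stands. In a run with outcome-dependent Liuzijue dropout and a true effect of 54 m, complete-case gave 68 m. Imputation gave about 65 m with an auxiliary variable correlated 0.5 with the outcome residual, and 59 to 60 m with one correlated 0.8 (both assumed). Agreement is therefore not inevitable, and step 5 shows that complete-case is not useless.

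A reader might go further and infer that modest informative dropout would overturn a positive result. Taking a standard error of 20 m and t = 1.999 (62 df), an observed 45 m effect appears to lose significance at (45 − 39.98)/(6/38) = 32 m, and a 54 m effect at 89 m. Those figures are inconsistent with the illustration. The 20 m ignores the assumed correlation of 0.7 and would be the standard error of the planned contrast only at a correlation of 0.5. At 0.7 the same formula gives, for a 45 m effect, about 89 m (change contrast) or 104 m (baseline-adjusted), and for a 54 m effect about 146 or 161 m. The documents give no correlation, so they support no particular tipping point. Nor do they show that dropout is, or will be, informative.

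**Conclusion.** The concern holds in a limited form. Neither named analysis relaxes missing at random, so neither can verify that the imputed result is robust to dropout that depends on the unseen week-13 outcome. When imputation uses only baseline and group, agreement with complete-case is built in for that kind of dropout. It is not built in when dropout depends on baseline or when informative auxiliary data are used.

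At the planned dropout, Liuzijue dropouts 30 to 80 m worse than predicted would mean an undetected overstatement of about 5 to 13 m, less than one standard error at the assumed correlation of 0.7. With 25% missing and an 80 m shortfall it would reach 20 m. These are illustrations of what the checks would miss, not estimates of bias in this trial. The matter is worth settling before the analysis planned for January 2027, but it does not by itself threaten the design.

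**What to change.** Prespecify a delta-adjusted multiple imputation of week-13 6MWT, analysed with the planned primary contrast. Shift the imputed values downward in the Liuzijue arm, and then in both arms, over a stated range that includes 30 and 54 m (the range of minimal clinically important differences quoted in the 6MWT section) and extends until the conclusion changes. Report the tipping point. State the missing-at-random assumption and the variables in the imputation model, including any auxiliary records.

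Keep complete-case as a descriptive comparison. Describe per-protocol as a supplementary analysis of a different question, and drop the statement that these two analyses verify the imputation.

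The cost is a sentence or two in the analysis section and a little extra programming. No new data, visits or participants are needed.

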### Randomization and Blinding

SPSS (version 27.0; IBM) will be used to generate a random number list. A block randomization algorithm will assign a unique random number to each participant, and this information will be kept strictly confidential. All random numbers will be sealed in opaque envelopes, and group allocation will be performed using the envelope method. After completing baseline assessments, trained researchers will randomly select envelopes to assign participants to either the control group or the Liuzijue group according to the numbers contained therein.

Given that this trial involves physical intervention, it is difficult to blind the participants. Therefore, independent outcome assessors who are not involved in participant recruitment, intervention delivery, or group allocation will be used. All outcome assessments will be conducted by these blinded assessors according to standardized procedures. In addition, data analysts will also be blinded to group allocation in order to minimize bias and enhance the reliability of the results.

If it becomes necessary to unblind the outcome assessors or data analysts, the reasons must be documented and reported in detail. During data analysis, appropriate statistical methods will be applied to control potential bias.

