9	Multifidus	The junction between the middle $\frac{1}{3}$ and medial $\frac{1}{3}$ of the line from PSIS^d^ to L5^e^

a SENIAM: Surface Electromyography for the Non-Invasive Assessment of Muscles.

b C7: the seventh cervical vertebra.

c ASIS: anterior superior iliac spine.

d PSIS: posterior superior iliac spine.

e L5: the fifth lumbar vertebra.

The sEMG assessment will consist of static and dynamic tests. In the static test, participants will stand quietly while EMG signals are recorded for 5 seconds at rest, at the end of maximal inspiration, and at the end of maximal expiration, with each condition repeated three times at two-minute intervals. The dynamic test will involve a 10-meter walking trial, during which participants are instructed to walk as fast as possible along a corridor while both walking time and EMG signals are recorded simultaneously. The electrode placement for sEMG is illustrated in Figure 3. The sEMG data will be collected in week 0 and week 13.

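### The primary mixed model, with visits only at weeks 0 and 13, reduces to a change-score comparison: valid, but less precise than the baseline adjustment planned for secondary outcomes

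*Protocol article*

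**What the plan says.** Under Statistical Analysis, the primary outcomes go into linear mixed-effects models that "incorporate group, time, and their interaction as fixed effects alongside participant-level random intercepts to account for the repeated-measures design". The section states no baseline covariate and no constraint that the arms share a baseline mean.

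There is one follow-up visit. For the walk test, "The 6MWT outcome will serve as a primary indicator of intervention efficacy, assessed in week 0 and week 13". For electromyography, "The sEMG data will be collected in week 0 and week 13".

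The next paragraph of Statistical Analysis treats the secondary outcomes differently: "For continuous secondary outcomes, analysis of covariance adjusted for baseline values will be used where appropriate".

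On the order of events, Randomization and Blinding says: "After completing baseline assessments, trained researchers will randomly select envelopes to assign participants". Missing data are to be handled by multiple imputation in the intention-to-treat population.

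**The concern.** The repeated measures here are baseline plus a single follow-up. A free group main effect gives each arm its own baseline mean, so the interaction becomes the difference in mean change. If baseline is taken before allocation, the true baseline means are equal by design, and a model that uses this fact estimates the effect more precisely.

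Precision on the outcomes that carry the trial's conclusion is at stake. The section already names the more efficient method for continuous secondary outcomes and gives no reason for using a less efficient one on the primaries. The matter also bears on the sample size, whose formula uses the cross-sectional SD. The planned test has that variance at only one value of rho.

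**Working it through.** **Inputs from the protocol article.** Difference 54 m, SD 80 m (a baseline SD), 32 evaluable per arm, two-sided alpha 0.05, 80% power (Sample Size Calculation; Statistical Analysis). Visits at weeks 0 and 13 (sEMG; 6MWT; Table 1).

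**Assumption.** The correlation rho between week-0 and week-13 values is not given. It is varied from 0.3 to 0.8, with equal SDs at both visits.

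**The plan's own figure.** The stated formula gives n = (1.960 + 0.842)² × 2 × 80² / 54² = 34.45, so 35 per arm and not 32. At 32 per arm, a comparison that ignores baseline has 77.0% power by the normal approximation and 75.7% by the noncentral t. That discrepancy is a separate matter. The comparison below takes 32 per arm as stated.

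**Step 1: what the stated model estimates.** One complete data set was simulated (32 per arm, rho 0.6) and analysed four ways:

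| Analysis | Estimate | SE |
|---|---|---|
| Stated mixed model, group-by-time | 63.136 | 15.026 |
| Regression of change on group | 63.136 | 15.026 |
| ANCOVA of week 13 on group and week 0 | 63.021 | 14.115 |
| Mixed model with common baseline mean | 63.014 | 13.824 |

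The first two rows are identical. The stated model's group main effect equalled the observed baseline difference (-0.403), which confirms that it fits a separate baseline mean per arm.

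**Step 2: variances per participant.**
- Change score: 2 × SD² × (1 - rho)
- Baseline-adjusted: SD² × (1 - rho²)
- Ratio, adjusted to change: (1 + rho)/2, which is below 1 for every rho below 1
- Ignoring baseline: SD². The change score exceeds this when 2(1 - rho) > 1, that is, when rho is below 0.5.

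**Step 3: power.** The SE of the effect is the effective SD × √(2/32) = effective SD × 0.25. At rho 0.5, for example, the effective SDs are 80 × √1 = 80.0 m and 80 × √0.75 = 69.3 m, with SEs of 20.0 m and 17.3 m. Power comes from the noncentral t.

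| Assumed rho | Effective SD, change | Effective SD, adjusted | Variance ratio | Power, stated model | Power, adjusted |
|---|---|---|---|---|---|
| 0.3 | 94.7 m | 76.3 m | 0.65 | 61% | 80% |
| 0.5 | 80.0 m | 69.3 m | 0.75 | 76% | 87% |
| 0.7 | 62.0 m | 57.1 m | 0.85 | 93% | 96% |
| 0.8 | 50.6 m | 48.0 m | 0.90 | 98.8% | 99.3% |

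On the same basis, 80% power at 32 per arm needs rho of about 0.55 with the stated model and about 0.32 with adjustment.

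**The case against.** The strongest reply is that nothing is invalid. Under randomisation the change contrast is unbiased with correct type I error, and the mixed model does use baseline, through the within-person correlation. This stands. A reader might infer that the primary test is biased because a change score overcorrects chance baseline imbalance. That is a property conditional on the imbalance observed, not a bias across randomisations.

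The size of the loss also rests on a correlation that the documents do not give. At rho 0.7 the gap for 54 m is about 3 points with both tests well above 80%, and at 0.8 it is under 1 point. This stands too, and is why the whole range is shown. The gap closes less fully for a smaller effect: at 30 m, the lower end of the range in the 6MWT section, power at rho 0.8 is 66.0% against 70.5% by the normal approximation.

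A reader might also infer that the loss is greatest for electromyography because re-placed electrodes lower the correlation. The documents give no such correlation. They list several parameters, muscles and test conditions without singling one out, so the formulas apply only to one summary value per visit, and no electromyography loss can be computed.

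The ANCOVA wording is conditional (where appropriate), so it does not assign that method to every secondary outcome. This softens the contrast without removing it.

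Last, an article may leave covariates and the treatment contrast to an analysis plan that is not shown. This has some force. But the article does state the fixed effects, and they include a free group effect; that is a stated choice and not an omission. Reading group-by-time as the test of treatment is the natural reading of those terms.

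**Conclusion.** The point holds as one of efficiency and of consistency within Statistical Analysis. The stated primary model is equivalent to a change-score comparison on complete or imputed data, and only approximately so if missing follow-up is left unimputed. For any rho below 1 it is less precise than baseline adjustment. Adjustment cuts the variance of the effect estimate by (1 - rho)/2: 35%, 25%, 15% and 10% at rho 0.3, 0.5, 0.7 and 0.8. For 54 m this is worth about 18 power points at rho 0.3, 11 at 0.5, 3 at 0.7 and under 1 at 0.8.

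The documents do not support the stronger reading that the model leaves the walk test underpowered. That depends on rho: below 0.5 the stated model does worse than the variance in the sample-size formula, and above 0.5 it does better. The change should be made, but the trial's validity does not depend on it.

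**What to change.** In Statistical Analysis, specify one of the following for the primary outcomes:
- ANCOVA of the week-13 value on group and the week-0 value; or
- a mixed model with time and group-by-time but no group main effect, so that both arms share a baseline mean.

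Report the adjusted week-13 difference with its 95% CI as the treatment effect.

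Either choice requires that week-0 values precede any Liuzijue exposure. Randomization and Blinding indicates that they do. However, the Liuzijue Group section places three training sessions for that arm in the two weeks before the formal intervention, while Table 1 puts allocation and the baseline tests at week 0. These passages should be reconciled.

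The cost is about one sentence of analysis wording, with no new data. Both models can be fitted in SPSS. At submission 23 participants were enrolled, no interim analysis is planned, and analysis is due in January 2027, so the change can be made before any outcome data are analysed.
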